## Abstract

**Background:**

After major abdominal surgery (MAS), 20 % of patients endure major complications, which require invasive treatment and are associated with increased morbidity and mortality. A quality control algorithm after major abdominal surgery aimed at early identification of patients at risk of developing major complications can decrease associated morbidity and mortality. Literature studies show promising results for C-reactive protein (CRP) as an early marker for postoperative complications, however clinical significance has yet to be determined.

**Methods:**

A multicenter, stepped wedge, prospective clinical trial including all adult patients planned to undergo elective MAS. The first period consists of standard postoperative monitoring, which entails on demand additional examinations. This is followed by a period with implementation of postoperative control according to the PRECious protocol, which implicates standardized measurement of CRP levels. If CRP levels exceed 140 mg/L on postoperative day 3,4 or 5, an enhanced CT-scan is performed.

Primary outcome in this study is a combined primary outcome, entailing all morbidity and mortality due to postoperative complications. Complications are graded according to the Clavien-Dindo classification. Secondary outcomes are hospital length of stay, patients reported outcome measures (PROMs) and cost-effectiveness. Data will be collected during admission, three months and one year postoperatively. Approval by the medical ethics committee of the VU University Medical Center was obtained (ID 2015.114).

**Discussion:**

the PRECious trial is a stepped-wedge, multicenter, open label, prospective clinical trial to determine the effect of a standardized postoperative quality control algorithm on postoperative morbidity and mortality, and cost-effectiveness.

**Trial registration:**

www.ClinicalTrials.gov, NCT02102217. Registered 5 February 2015.

**Electronic supplementary material:**

The online version of this article (doi:10.1186/s13063-015-0903-y) contains supplementary material, which is available to authorized users.

## Background

Major abdominal surgery (MAS) may be defined as a surgical resections performed on colorectal, hepato-pancreatico-biliary and upper gastrointestinal organs with either primary anastomosis and/or stoma. Around 20 % of all MAS patients have a major complication, which requires invasive treatment such as reoperation, percutaneous drainage and intensive care admission [1, 2]. Major complications further increase morbidity and mortality after MAS, leading to longer intensive care and hospital stay, unplanned open procedures, creation of stomas and possible increase in cancer recurrence rates and costs [3–5].

In current postoperative practice median time to clinical diagnosis of a postoperative complication is approximately 8 days [6–8]. A delay in diagnosis of complications increases morbidity and mortality related to major complications [9–11], whereas early diagnosis of postoperative septic complications, before clinical deterioration, is associated with a decrease in the associated morbidity and mortality [12, 13]. Early detection of septic complications is challenging and may (clinically, serologically and in imaging techniques) be hard to distinguish from the physiological and postoperative systemic inflammatory response syndrome (SIRS) [8, 14, 15]. Furthermore clinical risk assessment appears to have a low predictive value for major complications such as anastomotic leak [16]. This further stresses the need for a standardized quality control algorithm after MAS. Notably, there are currently no standard quality control tests or protocols available for use after MAS to differentiate between a normal and a complicated postoperative course.

Several biomarkers, such as Interleukin-6 (IL-6), tumor necrosis factor α (TNF-α), procalcitonin, white blood cell count (WBC) and C-reactive protein (CRP) [17], have been assessed in the search for a marker in the early diagnosis of postoperative complications. WBC does not significantly differ in patients with an uncomplicated versus complicated postoperative course. WBC is therefore not useful in a standardized quality control algorithm. Procalcitonin, IL-6 and TNF-α have been assessed as markers of postoperative sepsis [18]. However, compared to CRP they achieve similar results in predicting major complications after MAS. Moreover, taking into account the higher cost and limited availability of procalcitonin, IL-6 and TNF-α testing [19], further focus will be on the use of CRP in a postoperative standardized quality control algorithm.

CRP is well-established as a marker of infections and complications and has shown promising results [19, 20]. It is an acute-phase protein synthesized in the liver under stimulation of IL-6 and TNF-α in inflammatory processes, which amongst others enhances phagocytosis of bacteria by macrophages [21]. In healthy individuals, the CRP level is <1 mg/L. In mild inflammation it can rapidly reach over 40 mg/L and even levels >400 mg/L have been detected in severe inflammatory response, sepsis or burns [22]. CRP levels also increase as a consequence of operative trauma, and it is even suggested that the level of postoperative CRP is proportional to the length of the operation, amount of operative trauma and intra-operative complications [23]. A peak in postoperative CRP levels is observed 48 − 72 hours after surgery. In uneventful cases, the levels decrease after this peak [24]. Furthermore, the plasma half-life of CRP is 19 hours and postoperative CRP levels are independent of gender, age, body mass index (BMI), diet, diurnal rhythm or organ function [25]. Circulating CRP levels are therefore only determined by their rate of synthesis [26]. Based on these characteristics, CRP might be a promising valuable marker for grading inflammation related to postoperative complications.

Several studies have assessed the use of CRP as a marker for postoperative complications after MAS. Established cut-off CRP levels serving as markers for infective complications range from 140 mg/L to 170 mg/L on postoperative day (POD) 3 [27, 28]. In relation to anastomotic leakage in patients undergoing colorectal surgery, a cutoff for CRP of 190 mg/L on POD 3 and 125 mg/L on POD 4 has been proposed [29, 30]. The largest retrospective series included 1,187 patients who had undergone colorectal surgery, calculating a cutoff of 123 mg/L as a marker for all septic complications [20, 31], yet they did not differentiate between minor and major complications. A recent meta-analysis established a cutoff of 172 mg/L on POD 3 as a marker for anastomotic leakage [32]. Definitions for anastomotic leak vary widely in the literature [33], which limits reproducibility and excludes patients that require re-intervention for other complications. Therefore, our interest lies in diagnosing all major complications that require invasive treatment, as classified by grades 3 − 5 in the Clavien-Dindo classification [34, 35].

Based on our own retrospective data for 399 patients who underwent MAS, a level of 140 mg/L is proposed as cutoff for POD 3, 4 and 5 as a marker for major complications, with an overall sensitivity of 78.1 %, a specificity of 53.7 % and a negative predictive value of 89.1 %. This is in line with recent literature [2, 36].

Serum CRP is non-specific for location, thus, additional imaging is required. Computed tomography (CT) is the current imaging modality of choice. In our retrospective data, CT had sensitivity of 91.7 % and specificity of 100 % for diagnosis of major complications; this is confirmed in the literature [14, 37]. Moreover, in the study conducted by Eckmann et al. CT had sensitivity of 97 % [13]. Another recent study established CT as the preferred modality in diagnosis of anastomotic leakage [36].

In 2008, Den Dulk et al. implemented a standardized scoring system for the clinical status of patients undergoing colorectal surgery. With this system they decreased the time between surgery and diagnosis of anastomotic leakage from 8 to 6 days, thereby decreasing mortality from 39 % to 24 % (*p* = 0,24), further supporting the role of a standardized postoperative quality control algorithm following MAS [6, 7]. However the search for an optimal algorithm continues. CRP and CT scanning have been shown to differentiate between an uncomplicated and a complicated postoperative course. Currently their use is only on demand. The PRECious protocol presented here is a postoperative quality control algorithm, which is aimed at early diagnosis and treatment of patients with major complications.

## Methods

### Study objectives

The aim of this study is to evaluate the role of a standardized quality control algorithm after MAS in order to early diagnose and treat major complications and achieve safe discharge criteria. The PRECious trial is a prospective, multicenter, open, stepped-wedge study. All patients who are planned to undergo elective major digestive surgery, defined as any gastro-intestinal resection with reconstruction via anastomosis or stoma, will be included. Our hypothesis is that the standardized postoperative quality control algorithm will allow for early diagnosis and treatment of complications, thereby decreasing morbidity and mortality associated with MAS.

### Endpoints

The primary endpoint of the study consists of a combined endpoint entailing all morbidity and mortality due to major complications. Complications will be classified according to a modified Clavien-Dindo classification in two groups [34, 35]. Group I consists of grade I and grade II complications, which are classified as minor. Early detection of major complications that may require invasive treatment, such as re-laparotomy or percutaneous drainage and/or intensive care admission, which might even lead to death, as classified by Clavien-Dindo grades III, IV and V, is of major importance. The comprehensive complication index will also be calculated [38]. All mortality and morbidity after major complications will be recorded, entailing fistula; bowel obstruction or herniation; abscesses; wound dehiscence; abdominal compartment syndrome; unplanned enterostomy; enterostomy dysfunction; myocardial infarction; pulmonary embolism; respiratory insufficiency; urosepsis; cerebrovascular accident; bleeding, and anastomotic leak.

Secondary endpoints will be patient-related outcome measures (PROMs), measured with the EuroQol-5D (EQ-5D) and gastrointestinal quality of life index (GIQLI) questionnaires. Furthermore postoperative recovery data will be collected in both groups, such as length of hospital stay and intensive care length of stay. Alongside the trial a cost-effectiveness analysis will be conducted.

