### Power of the study

Based on retrospective data of 399 patients who underwent MAS, we assessed all mortality and morbidity due to major complications (multiple reoperations, multiple percutaneous drainages, enterostomy during re-intervention) and found this to be 17 %. Based on the results of den Dulk, who report a decrease in mortality following implementation of a clinical item scoring list, we calculated the following sample size [6]: a group sample size of 525 in group 1 and 525 in group 2 to achieve 80 % power to detect a difference in frequency of morbidity in the control group, which is 17 %, in comparison to the PRECious group, with an expected morbidity of 11 %. The test statistic used is the two-sided Mantel-Haenszel test. The significance level of the test was targeted at 0.05.

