#### PRECious group

The second period will be considered the intervention group. All patients will be allocated to postoperative controls according to the PRECious protocol. Within this protocol peripheral blood samples for CRP measurements will be collected routinely on POD 2, 3, 4 and 5. If CRP exceeds 140 mg/L on the third, fourth or fifth POD, enhanced CT of the abdomen will be conducted within 24 hours. It is expected that two thirds of patients will undergo CT versus one third of the control group. Intravenous contrast is administered, with regard to renal function, to conduct CT. Depending on the organ undergoing surgery, oral or rectal contrast will be administered, for which the patient will have to drink oral contrast or receive rectal administration prior to CT. After the first postoperative week, CRP samples will be collected on demand, according to the consulting physician. If a major complication is diagnosed, immediate treatment will be commenced as soon as possible and as appropriate. All major complications are to be confirmed in reoperation or suspicious drain fluid upon percutaneous drainage and culture.

To allow for correct implementation of the protocol a transition period of month is deemed necessary before starting measurements in the intervention group. A flow-chart depicting the design of the study is displayed in Fig. 1.

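### The primary endpoint is stated with different scopes, and the 17% planning rate, and so the 80% power, belongs to the narrowest of them

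*Protocol article*

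**What the plan says.** The primary endpoint is described in three places.

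- **Abstract, Methods:** a combined outcome "entailing all morbidity and mortality due to postoperative complications". No severity limit is given.
- **Endpoints:** "The primary endpoint of the study consists of a combined endpoint entailing all morbidity and mortality due to major complications". The section describes major complications through the interventions that they may need and by grade: "such as re-laparotomy or percutaneous drainage and/or intensive care admission, which might even lead to death, as classified by Clavien-Dindo grades III, IV and V". The text continues "All mortality and morbidity after major complications will be recorded, entailing fistula", and the list that follows includes abscesses, bleeding and anastomotic leak.
- **Power of the study:** almost the same label as in Endpoints, but with a parenthesis naming "multiple reoperations, multiple percutaneous drainages, enterostomy during re-intervention". The 17% control rate was found for this in 399 retrospective patients. The target is 11%, with 525 per group, 80% power and a two-sided 0.05 level.

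Three other places bear on the point. The Background puts major complications at around 20%, and gives the accuracy of CRP for major complications in the authors' own 399 patients: sensitivity 78.1%, specificity 53.7%, negative predictive value 89.1%. The PRECious group section says "It is expected that two thirds of patients will undergo CT versus one third of the control group", and has major complications confirmed at reoperation or through drain fluid. The section on patient allocation and design states that blinding is not possible.

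**The concern.** The three descriptions can give different event counts from the same patients. A patient with one abscess, drained once, has a grade III complication. That patient can be counted under the abstract and Endpoints wording, but does not meet the parenthesis in the Power section, which requires repeated procedures or a stoma.

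Two things follow. First, the sample size is justified for one event definition, while the Endpoints section can be followed with another. The choice between them could then be made after the data are seen. Second, the definitions differ in how far the intervention can affect the count. The stated hypothesis is that earlier diagnosis and treatment reduce the harm that follows. If a first drainage or reoperation is itself the event, a protocol that doubles CT use can add events in its own group while doing what it is meant to do.

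**Working it through.** **1. Reproduce the plan's figure.** For 17% versus 11% (mean 14%), pooled variance under the null and no continuity correction:

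n = [1.96·√(2·0.14·0.86) + 0.8416·√(0.17·0.83 + 0.11·0.89)]² / 0.06² = (0.9618 + 0.4115)² / 0.0036 = 524 per group.

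The plan states 525, at which power is 80.1%. The arithmetic is sound for these rates.

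**2. Is 17% the rate of all major complications?** With prevalence p, negative predictive value = spec(1−p) / [spec(1−p) + (1−sens)p]. Solving for p with the Background's figures:

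p = 0.537·0.109 / (0.537·0.109 + 0.891·0.219) = 0.0585 / 0.2537 = 23.1%.

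Rounding of the inputs moves this only between 23.0% and 23.2%. In 399 patients it is about 92, against about 68 at 17%. Conversely, at p = 17% the negative predictive value would be 0.4457 / (0.4457 + 0.0372) = 92.3%, not 89.1%. The Background separately gives around 20%. So 17% sits below both of the document's figures for all major complications.

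**3. Power at 525 per group on a grade III–V incidence endpoint.** Power = Φ{[d − 1.96·√(2p̄(1−p̄)/525)] / √[(p₁(1−p₁) + p₂(1−p₂))/525]}, where d = p₁ − p₂ and p̄ is their mean. The planned relative risk is 0.11/0.17 = 0.647.

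| Control rate | What is kept | PRECious rate | Power | n per group for 80% |
|---|---|---|---|---|
| 20% | 6-point drop | 14% | 73.6% | 615 |
| 23% | 6-point drop | 17% | 68.1% | 697 |
| 20% | relative reduction | 12.9% | 87.0% | 433 |
| 23% | relative reduction | 14.9% | 92.0% | 365 |

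**4. Assumed scenario: extra counted events in the PRECious group only.** The documents give no size; 1 to 3 points (about 5 to 16 of 525 patients) is an assumption.

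| Starting contrast | +1 point | +2 points | +3 points |
|---|---|---|---|
| 20% vs 14% | 56.8% | 39.2% | 23.9% |
| 23% vs 17% | 51.9% | 35.6% | 21.8% |
| 20% vs 12.9% | 74.4% | 57.9% | 40.2% |

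An excess of 6 points would cancel a 6-point drop.

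**The case against.** The strongest reply is that the Endpoints and Power sections share nearly the same label. Endpoints speaks of morbidity caused by, or following, major complications, which fits a reading as consequences. Its list is introduced as what will be recorded, so it may be a data-capture list. The abstract's omission of a severity limit may be loose wording. This stands in part: Endpoints does not say outright that incidence of grade III–V complications is the endpoint. But it does not exclude that reading either, and its list does not match the Power section's parenthesis.

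The parenthesis could also be read as examples. Read strictly, 17% against 23% means that about 74% of patients with a major complication (17/23) met the narrower definition, a high share that nothing in the document confirms. The 20% is a rounded background rate. The 23% assumes that the two mentions of 399 patients are the same cohort and that the accuracy figures cover all of them. Even so, if the parenthesis were only examples, 17% would have to be the rate of all major complications, and the accuracy figures do not allow that under the same assumptions.

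A reader might infer that the wider endpoint must show no benefit or harm. The documents do not support that. Controls are diagnosed clinically at a median of about 8 days, morbidity is listed at discharge, 3 and 12 months in both groups, CT specificity was 100% in the authors' data, and confirmation at reoperation or drainage is required. Much of what CT finds may be the same events found sooner.

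**Conclusion.** The inconsistency is in the text, and it concerns the outcome on which the trial's conclusion rests. The 80% power belongs to 17% versus 11% on the Power section's definition and does not carry over to grade III–V incidence. There, 525 per group would give about 68–74% power with the 6-point drop kept and 87–92% with the relative reduction kept. The second case needs the algorithm to cut the incidence of major complications by about a third.

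It would go too far to call the sample size wrong, or the trial underpowered in every reading: 525 reproduces, and the wider endpoint could have more power. It would also go too far to treat detection bias as established. The mechanism follows from the expected CT use (two thirds versus one third), the open-label design and the way complications are confirmed, but its size is not given. The 22–57% power range is conditional on an assumed excess of 1 to 3 points with the 6-point drop kept.

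**What to change.** State one primary endpoint, in the same words, in the abstract, Endpoints and Power sections: the definition that produced 17%. Count each patient once, yes or no, for death due to a major complication, more than one reoperation, more than one percutaneous drainage, or enterostomy at re-intervention. Use the same follow-up window in both groups; the 3-month visit, already planned for both, is one option. If the full protocol already fixes the counting rule and window, the article need only agree with it. Make grade III–V incidence, anastomotic leak and abscess secondary, and say that the Endpoints list is for data capture.

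The cost is wording. Morbidity is already recorded in both groups, the sample size stands, and the Trial status section says recruitment has not begun. The downside is a narrower main endpoint. It still counts repeated drainages and stomas, which are unblinded decisions that can follow a protocol CT, so it is less exposed to detection but not immune. Reporting grade III–V incidence beside it would let readers see any such effect.

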### Data collection and statistics

Data will be collected partially by means of a secured Internet module and partially by hard-copy datasheets. The secured online module is especially designed for the PRECious trial. Hard-copy datasheets, such as completed quality of life questionnaires will be sent to the VU medical center by mail, were they will be kept in a secured room. Data will be collected daily until discharge. PROMs will be collected preoperatively, and at 5 days, 3 months and 12 months postoperatively. A study chart for measurements is depicted in Table 1.

**Table 1 Tab1:** Study measurements

	Study period										
	Enrolment	Allocation	Post-allocation								Close-out
Time point	Pre-operative	Pre-operative	Surgery	POD 2	POD 3	POD 4	POD 5	Discharge	3 Mo	12 Mo	t_x_
Enrolment											
Eligibility screen	X										
Informed consent	X										
Allocation		X									
Interventions											
Control group		X									
CRP measurement				X	X	X	X				
QOL questionnaire		X					X		X	X	
PRECious group											
CRP measurement				X	X	X	X				
CT if CRP >140 mg/L					X	X	X				
QOL questionnaire		X					X		X		
Assessments											
Control group											
List baseline variables		X									
List operative data			X								
List admission data								X			
Quality of life		X					X		X	X	
List morbidity								X	X	X	
List survival								X	X	X	
PRECious group											
List baseline variables		X									
List operative data			X								
List admission data								X			
Quality of life		X					X		X	X	
List morbidity								X	X	X	
List survival								X	X	X	X

*POD* postoperative day, *Mo* months, *CRP* C-reactive protein, *CT* computed tomography scan, *QOL* Quality of Life, T_x_ end of protocol

One research fellow in the VU medical center will monitor the data for all included patients, and maintain regular contact with all participating centers. Due to the nature of the study the researcher cannot be blinded, hence an external monitoring committee (Clinical Research Bureau, Amsterdam, Netherlands) is installed and will assess data collection. All required parameters will be collected in an SPSS data file. Data analysis will be performed according to the intention-to-treat principle. Continuous variables will be compared using the *t* test or Mann-Whitney *U* test, as appropriate. Frequencies will be compared using the Chi-square or McNemar tests, as appropriate.

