### Economic evaluation

Direct medical costs, non-medical costs and time-cost differences will be calculated for each arm of the study. These will include the increased costs in the PRECious arm due to the extra CRP testing and greater use of CT, and costs due to complications and readmissions. We expect admission duration to be shorter in the PRECious arm due to early diagnosis and treatment of complications. Therefore, the protocol committee deems the protocol cost-effective. On retrospective analysis of direct medical costs in patients who underwent MAS the average cost was 8.584,81 € (95 % CI 8.332,51 − 8.860,81 €) in patients without complications, 15.412,96 € (95 % CI 14.250,22 − 16.708,82 €) after minor complications, and 29.198,23 € (95 % CI 27.187,13 − 31.295, 78 €) in patients with a major complication that required invasive treatment (*p* <0.001) [5].

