#### Postoperative management

Besides differences in postoperative controls, postoperative management will be similar in both groups. Early mobilization will be encouraged, starting with sitting out of bed the first day postoperatively. A dietician will monitor intake. Patients will be discharged when they pass stools, are able to drink and eat sufficiently and are comfortable with oral analgesia. Follow up will be scheduled at the outpatient clinic 3 and 12 months after the index operation. Here PROMs will be collected and morbidity monitored.

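### Table 1 schedules admission data at discharge only, so length of stay, read naturally, omits readmission days and can understate, or under some assumptions reverse, the effect of PRECious on hospital use

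*Protocol article*

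**What the plan says.** The abstract states: "Secondary outcomes are hospital length of stay, patients reported outcome measures (PROMs) and cost-effectiveness". The Endpoints section lists recovery data "such as length of hospital stay and intensive care length of stay". Neither place says whether stay means the index admission or all admissions, over what period it runs, or how a patient who dies is scored.

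Under Data collection and statistics, the text says "Data will be collected daily until discharge". In Table 1 the row "List admission data" is marked at discharge only, in both groups. The morbidity and survival rows are marked at discharge and again at 3 and 12 months. Continuous variables are to be compared by t test or Mann-Whitney U test.

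Readmissions appear in the Economic evaluation, as a cost item for each arm. The same section says: "We expect admission duration to be shorter in the PRECious arm due to early diagnosis and treatment of complications". It gives that expectation as the reason to regard the algorithm as cost-effective.

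**The concern.** The intervention changes when complications are found. The Background puts current practice at a "median time to clinical diagnosis of a postoperative complication is approximately 8 days". Under PRECious, "peripheral blood samples for CRP measurements will be collected routinely on POD 2, 3, 4 and 5", and a value above the cutoff on day 3, 4 or 5 leads to CT. The discharge rule, common to both periods, is functional: "Patients will be discharged when they pass stools, are able to drink and eat sufficiently and are comfortable with oral analgesia". A control patient can meet it before a complication is recognised, go home and be readmitted.

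On index stay that patient scores a short stay, and the readmission days are lost. The same patient diagnosed before discharge under PRECious contributes the whole course. If PRECious moves diagnoses from after discharge to before it, index stay counts against the algorithm something it is meant to achieve. At stake is the reading of a named secondary outcome, and of the expectation of a shorter admission. The primary endpoint is not affected.

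**Working it through.** The protocol gives no figure for length of stay, so there is none to reproduce. The check asks how far index stay and total hospital days can diverge. The only document input is the major complication rate of about 20% (Background). All stays, missed shares and mortality rates below are assumptions, except where a source is named.

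**1. General relation.** Let s_C and s_P be the shares of complicated patients diagnosed after discharge in the control and PRECious periods, and R the mean readmission length. Differences are PRECious minus control, per complicated patient:

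total-days difference = index difference + R × (s_P − s_C)

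If the shares are equal, the two measures agree. If PRECious lowers the share, index stay hides R × (s_C − s_P) days of benefit.

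**2. Illustration A.** A complication found in hospital means 28 days in control and 24 under PRECious. A missed one means 6 index days plus 20 readmission days. PRECious halves the missed share m.

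- Index: control 28(1 − m) + 6m = 28 − 22m; PRECious 24(1 − m/2) + 6(m/2) = 24 − 9m; difference −4 + 13m.
- Total: control 28(1 − m) + 26m = 28 − 2m; PRECious 24(1 − m/2) + 26(m/2) = 24 + m; difference −4 + 3m.

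| Missed share in control | Index difference (days) | Total difference (days) |
|---|---|---|
| 20% | −1.4 | −3.4 |
| 40% | +1.2 | −2.8 |
| 60% | +3.8 | −2.2 |

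The index difference is zero at m = 4/13, about 31%. With an in-hospital saving of 2 days instead of 4, it is −2 + 12m, which is zero at about 17%.

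The trial compares all patients, not only complicated ones. At a 20% complication rate the 40% row becomes 0.2 × 1.2 = +0.24 index days and 0.2 × (−2.8) = −0.56 total days per enrolled patient.

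**3. Illustration B, with other assumptions, per enrolled patient.** Index stay is 22 days in control for a complication found in hospital, 2 days less under PRECious, and 6 days if missed. The complication rate is 20%.

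| Missed share, control to PRECious | Readmission (days) | Index difference | Total difference | Opposite signs |
|---|---|---|---|---|
| 5% to 5% | 20 | −0.38 | −0.38 | no |
| 10% to 5% | 20 | −0.22 | −0.42 | no |
| 20% to 5% | 20 | +0.10 | −0.50 | yes |
| 30% to 5% | 20 | +0.42 | −0.58 | yes |
| 30% to 5% | 8 | +0.42 | +0.02 | no |

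Third row in full: control index 0.8 × 22 + 0.2 × 6 = 18.8; PRECious 0.95 × 20 + 0.05 × 6 = 19.3; 0.2 × 0.5 = +0.10. Adding readmissions gives 22.8 and 20.3; 0.2 × (−2.5) = −0.50.

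**4. Death.** Suppose death is scored as a 10-day stay, survivors of a major complication stay 22 days in control, and PRECious saves 2 days. If mortality among them is 10% in both periods, the difference is −0.36 days per enrolled patient. If it is 10% in control and 6% under PRECious, the difference is −0.28, so lower mortality hides 0.08 days. With 39% and 24%, the mortality rates of the leakage-score study cited in the Background, taken as an upper case, it is +0.06.

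**The case against.** The strongest reply is that the article nowhere confines length of stay to the index admission. Table 1 is a form schedule, the abstract says data are also collected at three months and one year, and a condensed article may leave counting windows and death rules to the full protocol. That stands in part: index stay is an inference. It is still the natural one, because the table repeats morbidity and survival at later visits and does not repeat admission data.

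A reader might go further and infer that the comparison is biased and will show the wrong sign. The documents do not support that. They give no share of complications found after discharge, no readmission length and no in-hospital saving. The figure of about 8 days to diagnosis does not say that patients were already home. Several scenarios above show no reversal.

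A reader might also infer that hospital use is otherwise ignored, or that excess deaths could pass as a benefit. Readmission costs are counted for each arm, so the cost-effectiveness result does not rest on index stay. Mortality is part of the primary endpoint, and survival is recorded at three time points.

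Finally, one might argue that sampling to day 5 holds patients who are fit to go home and so distorts the outcome. No section requires a stay until day 5, the discharge criteria are common to both groups, and Table 1 marks CRP on the same days for controls. Any such delay would in any case be a real effect of the algorithm, which length of stay ought to show.

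**Conclusion.** The point holds as a weakness in how a secondary outcome is measured. On the natural reading of Table 1, length of stay omits readmission days. Because PRECious is designed to change when complications are found, the omission may not be equal in the two periods. The result can understate the effect on hospital use, and in Illustration A it reverses only if more than about 31% of complicated control patients are diagnosed after discharge. That threshold moves with the assumed stays and saving, so reversal is possible and not demonstrated. At a 20% complication rate the divergence is a fraction of a day per enrolled patient: +0.24 against −0.56 days at a 40% missed share. The missing rule for death adds little at low mortality. The change is worth making because it is cheap and recruitment had not begun.

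**What to change.** Keep index stay as a descriptive measure. Make the hospital-use outcome one of these, within a fixed 90 days from surgery:

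- total hospital days, index admission plus readmissions; or
- days alive and out of hospital, with days after death counted as zero.

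The second deals with readmission and death together. If total days is chosen, report deaths beside it, because an early death still gives few hospital days. State in advance whether planned readmissions count. Use a fixed day 90 and not the visit date, which varies between patients.

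In Table 1, mark readmission and discharge dates at the 3-month visit in both groups. The readmission data are already needed for the Economic evaluation, and survival is already listed at 3 months. The cost is slightly more data entry and less direct comparability with published index stays, which the descriptive measure partly restores.
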